#### Sample size and power evaluation

Justification of the sample size is based on two-level hierarchical mixed-effects logistic regression. The analysis aims to compare the abstinence rate at 6 months post-intervention among the three intervention arms. In this design, the subjects are the level 1 units, and the centers are the level 2 units. All subjects in a particular center receive one of the possible interventions selected at random. Power is evaluated based on the differential effect size between the AAC + NRT and AAC arms, which is expected to be the smallest difference in the abstinence rate. Sample sizes of 480 in the AAC + NRT arm and 480 in the AAC arm, which are obtained by sampling 8 centers per arm with an average of 60 subjects per center, achieve 84% power to detect a difference in the abstinence proportions of 12%. The abstinence proportion at 6 months among AAC + NRT participants is assumed to be 32% under the alternative hypothesis, while the proportion among AAC participants is 20%. The test statistic used is the effect regression coefficient from a mixed-effects logistic regression model. The intra-cluster correlation coefficient is assumed to be 0.01 [29, 30], and the significance level of the test is 0.017 after Bonferroni adjustment. Considering the expected low abstinence rate in the AAA arm and a significant difference compared to both the AAC alone and AAC + NRT arms, and weighing ethical considerations to offer the more intensive intervention when possible, 240 subjects (an average of 30 subjects) per center from 8 centers will be necessary for the AAA arm to achieve more than 85% power with a 0.017 significance level. A total of 1,200 subjects will be necessary: 480 subjects (AAC + NRT; 60 subjects from 8 centers); 480 subjects (AAC; 60 subjects from 8 centers), and 240 subjects (AAA; 30 subjects from 8 centers). Considering a 20% drop-out rate, 1500 subjects will be enrolled.

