#### Analysis

All analyses in aim 2 will account for the multi-level nature of the group-randomized trial (i.e., patients nested within centers). Generalized linear mixed-effects models (GLMM) will form the basis of comparisons across intervention arms, including a random effect for the center. Models of binary outcomes (primary outcome and other cessation outcomes) will use a logit link to estimate relative risks to compare arms; models of continuous outcomes (e.g., quit attempts) will use an identity link assuming a Gaussian distribution, which will be verified to compare means. While balance across arms is expected, we will examine other covariates in the models as necessary, including sex as a biological variable. We will conduct pairwise comparisons to evaluate significant differences between arms, adjusting for multiple comparisons via the step-down Bonferroni method. The multi-level GLMM approach will also be used to evaluate the interventions’ causal direct and indirect effect estimates with mediator variables. Causal mediation analysis will be conducted to decompose the effects of mediators: total effect on the odds ratio scale = direct effect × indirect effect; total effect on the excess relative risk (ERR) scale = direct effect + indirect effect; and proportion mediated on the ERR scale = indirect effect/total effect × 100% using the counterfactual framework [38–42]. SAS CAUSALMED procedure will be used to estimate causal mediation effects. All causal models will include moderator variables. A sensitivity analysis will evaluate if the intervention effects differ by smoking type (cigarettes and waterpipe). The intra-cluster correlation coefficient will be estimated from the final model to inform future research.

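### At 20% to 32% abstinence, excess relative risks built from logistic odds ratios overstate the total and indirect effects in the mediation analysis

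*Protocol article*

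**What the plan says.** Protocol article, Approach for Aim 2, Analysis: binary outcomes, including the primary one, are modelled with a logit link. The mediation analysis is placed in the counterfactual framework. The total effect is a product of direct and indirect effects on the odds-ratio scale and a sum on the other scale: "total effect on the excess relative risk (ERR) scale = direct effect + indirect effect". The proportion mediated is the indirect share of the total on the ERR scale. On software, "SAS CAUSALMED procedure will be used to estimate causal mediation effects". The section mentions no rare-outcome condition, log link or risk-based calculation for this analysis.

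Protocol article, Sample size and power evaluation: "The abstinence proportion at 6 months among AAC + NRT participants is assumed to be 32% under the alternative hypothesis". For the AAC arm the planning figure is 20%. For the third arm there is only a qualitative statement: "Considering the expected low abstinence rate in the AAA arm".

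The Measures section lists risk perceptions, self-efficacy and social norms as patient-level mediators. It gives no expected mediator effect, standard deviation or share mediated.

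**The concern.** An excess relative risk is a risk ratio minus one. Regression-based mediation with a logit outcome model yields odds ratios conditional on the mediator. If the ERR parts are formed as (direct OR − 1) and direct OR × (indirect OR − 1), they approximate the counterfactual ERR parts only when the outcome is rare. The trial's own planning rates are not rare.

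Two things go wrong at such rates. The odds ratio lies further from one than the risk ratio, and the mediator-conditional odds ratios do not collapse to the marginal one. Standardizing only the primary arm effect would leave both problems in the mediation results.

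At stake is the size of the reported indirect effect, which is the main product of a mediation analysis. A reader would also see a total ERR of about 0.9 to 1.1 for a comparison whose risks imply 0.60.

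**Working it through.** **Inputs from the protocol (Sample size and power evaluation).** Abstinence 20% (AAC) and 32% (AAC + NRT); 480 per arm in 8 centers of 60; ICC 0.01; significance level 0.017; stated power 84%.

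**Inputs assumed, because the protocol gives none.** Mediator distribution, arm effect on the mediator, mediator effect on abstinence, no arm-by-mediator interaction, and the AAA abstinence rate.

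**1. The plan's own figure.** The inputs are "The intra-cluster correlation coefficient is assumed to be 0.01" and "the significance level of the test is 0.017 after Bonferroni adjustment". Design effect 1 + 59 × 0.01 = 1.59; effective n = 480/1.59 = 301.9 per arm. A two-sided test of 32% against 20% at 0.017 has 83.7% power (pooled variance) or 84.3% (unpooled). This agrees with "8 centers per arm with an average of 60 subjects per center, achieve 84% power", so 20% and 32% are the rates the design rests on.

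**2. Total effect, using only the plan's rates.**
- RR = 0.32/0.20 = 1.60, so ERR = 0.60.
- OR = (0.32/0.68)/(0.20/0.80) = 1.88, so OR − 1 = 0.88.
- Overstatement: 0.88/0.60 = 1.47 times.

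**3. Formulas for the split.** Let p00 = 0.20, p11 = 0.32, and p10 be the risk under the more intensive arm with the mediator at its comparator-arm distribution.
- True: indirect ERR = (p11 − p10)/p00; proportion mediated = (p11 − p10)/(p11 − p00).
- From logistic odds ratios: indirect ERR = direct OR × (indirect OR − 1); total ERR = direct OR × indirect OR − 1.

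**4. Mediator with negligible variance, half of the log odds ratio mediated.** Direct OR = indirect OR = √1.88 = 1.37. Then p10 = 0.25 × 1.37/(1 + 0.25 × 1.37) = 0.255.
- Indirect ERR from odds ratios: 1.88 − 1.37 = 0.51. True: (0.32 − 0.255)/0.20 = 0.32. Ratio 1.58.
- Proportion mediated: 0.51/0.88 = 57.8% against 53.8%.
- For 10% to 100% of the log odds ratio mediated, the ratio runs from 1.70 down to 1.47.

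**5. Normal mediator, integrated numerically with the marginal risks held at 20% and 32%.** Example: log-odds 0.7 per SD and an arm shift of 0.3 SD. Indirect OR = exp(0.21) = 1.234, direct OR = 1.614, p10 = 0.280.
- Total ERR: 1.614 × 1.234 − 1 = 0.99, against 0.60.
- Indirect ERR: 1.614 × 0.234 = 0.38, against 0.20.
- Proportion mediated: 38.0% against 33.5%.
- Fitting both regressions to 400,000 simulated patients with these values gave a formula total OR of 1.99 against an observed 1.88.

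**6. Ranges.**

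| Contrast and mediator | Indirect ERR, ratio to true | Proportion mediated, points too high |
|---|---|---|
| 20% vs 32%, binary mediator | 1.36–1.72 | about 0–4 |
| 20% vs 32%, normal, 0.3–1.0 log-odds per SD, shift 0.2–0.5 SD | 1.70–2.15 | 2–6 |
| 20% vs 32%, normal, 1.5 per SD | 2.41–2.77 | 5–7 |
| assumed AAA 10% vs AAC 20%, normal grid of row 2 | 1.40–1.71 | 1–5 |
| assumed AAA 5% vs AAC 20%, normal grid of row 2 | 1.48–1.92 | 1–7 |
| 2% vs 3.2% (rare-outcome control), normal grid of row 2 | 1.04–1.10 | under 1 |

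Over row 2 the total ERR is 0.90 to 1.10. The bias nearly disappears in the last row, so outcome frequency is the cause.

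**7. Odds-ratio scale.** With half of the log odds ratio mediated, the indirect OR by formula against the exact value is 1.37 vs 1.37 (negligible variance), 1.40 vs 1.37 (0.6 per SD) and 1.45 vs 1.37 (1.0 per SD).

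**The case against.** The strongest reply is that nothing quoted is false. The product and sum identities hold exactly for counterfactual effects at any outcome rate, and the protocol invokes the counterfactual framework. It does not write out the odds-ratio-based ERR formulas, and it does not say how the named procedure computes ERR. An article can leave estimator options to a fuller plan. This stands, and it makes the point conditional: the error arises if the ERR parts are taken from logistic odds ratios. The point survives because the article does commit to a logit link, to OR and ERR scales and to a named procedure, and nothing in it steers the analyst away from that route at 20% to 32% abstinence.

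Several stronger readings are tempting and are not supported:

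- A reader might infer that the indirect effect is nearly doubled. That needs a fairly strong normal mediator, and the protocol gives no mediator strength.
- A reader might infer that the proportion mediated is badly wrong. Numerator and denominator inflate together, so the error is usually small and can vanish (90.1% against 90.4% in one binary-mediator case).
- A reader might carry the 20% vs 32% figures to every contrast. That contrast isolates NRT, which the Hypotheses section ties to withdrawal. Norms and self-efficacy are tied to AAC, so AAC against AAA is the more relevant contrast, and no AAA rate is given.
- A reader might infer that the mechanism hypotheses will be decided on these figures. The Analysis section sets no test or threshold on the ERR or on the proportion mediated.

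**Conclusion.** The point holds in a limited form. The plan pairs a logit outcome model with an ERR decomposition at abstinence rates where odds ratios cannot stand in for risk ratios, and it states no safeguard. If the ERR parts come from logistic odds ratios, the total ERR for 20% vs 32% is 0.88 to 1.10 instead of 0.60. The indirect ERR is then roughly 1.4 to 2.1 times too large for moderate mediators, and more for stronger ones. The lower end of the total follows from the protocol's rates alone. Everything else rests on assumed mediator strength and no arm-by-mediator interaction.

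The proportion mediated is a lesser concern at about 0 to 6 points, as is the odds-ratio split. The primary comparison and the sample size are not touched. This should be corrected before analysis, but it does not threaten the trial's main conclusion.

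**What to change.** In Approach for Aim 2, Analysis, state that natural direct and indirect effects on abstinence will be estimated either with a log-link outcome model or by standardization (g-computation or simulation from the fitted mediator and outcome models). Report them and the proportion mediated on the risk-ratio/ERR or risk-difference scale. State that ERR components derived from logistic odds ratios will not be reported. The sum identity can stay, since it is correct for risk-based quantities.

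The cost is a change of wording and a little extra programming; no new data are needed. A log-link model may fail to converge, which standardization avoids.

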#### Measures

Measures for aim 2 are summarized in Table 2. Research assistants will administer the screener and baseline survey at the time of enrollment in the center. Follow-up assessments at 1 and 3 months will be completed by the counselor via telephone. The 6-month assessment will be completed in-person, at the center, by the research assistant to validate self-reported abstinence. All patient assessments will be administered using REDCap.The primary outcome is the 7-day point prevalence (defined as any smoking, even a puff) carbon monoxide-confirmed (< 8 ppm) smoking abstinence assessed at 6-month follow-up, in line with recommendations from the Society for Research on Nicotine and Tobacco for assessing outcomes in smoking cessation trials [31].Other cessation outcomes: we will include self-reported measures for continuous abstinence between baseline, 3 months, and 6 months; 24-h quit attempts; and reduction in smoking at 1, 3, and 6 months [31].Multi-level mediators and moderators: patient assessments will also collect data on potential mediators (risk perceptions [32], self-efficacy [33], and social norms [34]), and moderators (age, sex, education, cigarettes/waterpipe per day, nicotine dependence [35], and prior quit attempts). Provider assessments will also collect data on center characteristics (e.g., priority, climate) and provider knowledge, attitudes, and self-efficacy [36, 37].Cost: we will collect data on estimates of the time spent delivering the interventions using the provider surveys and counselor electronic logs. We will develop templates to capture these data prospectively and improve cost assessment accuracy. We will assess costs to deliver the interventions, including personnel resources based on MoPH salaries, NRT, educational materials, and technology costs. Costs of developing training materials will also be included. Any hardware and material costs necessary for implementing the interventions will be tracked through invoices. Intervention costs will exclude research costs.

**Table 2 Tab2:** Aim 2 evaluation

	Measures description	Instrument/data source	Timing
Primary outcome	Carbon monoxide-confirmed abstinence	Follow-up patient visit	6 months
Other cessation outcomes	Continuous abstinence, quit attempts, smoking reduction	Phone assessment	1, 3, 6 months
Patient-level mediators	Risk perceptions, self-efficacy, social norms	Phone assessment	0, 1, 3, 6 months

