Provider-level mediator	Provider behavior, delivery of AAA, AAC	Patient survey	Index visit
Patient-level moderators	Age, sex, education, cigarettes/waterpipes per day, nicotine dependence, prior quit attempts	Patient survey	Index visit
Clinic- and provider-level moderators	Clinic characteristics (priority, climate), provider knowledge, attitudes, self-efficacy	Provider interview/survey	Pre-trial
Cost	Intervention delivery costs	Cost survey/electronic log	Trial

*AAA* Ask, Advise, Assist, *AAC* Ask, Advise, Connect

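### The covariate rule for the causal mediation models does not name the month-0 value of the patient-level mediators, although it is collected, so the indirect effects can be confounded

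*Protocol article*

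**What the plan says.** The Aim 2 Analysis section of the protocol article specifies the mediation analysis in some detail. It uses a counterfactual decomposition on the odds-ratio and excess-relative-risk scales and reports a proportion mediated. It also names the software: "SAS CAUSALMED procedure will be used to estimate causal mediation effects". The one covariate statement specific to these models is "All causal models will include moderator variables".

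Table 2 defines the moderators. At patient level they are "Age, sex, education, cigarettes/waterpipes per day, nicotine dependence, prior quit attempts", taken at the index visit. At clinic and provider level they are "Clinic characteristics (priority, climate), provider knowledge, attitudes, self-efficacy", taken before the trial; the self-efficacy in that second list is the provider's.

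The patient-level mediators in Table 2 are "Risk perceptions, self-efficacy, social norms", scheduled at 0, 1, 3 and 6 months. A month-0 score is therefore collected for each, but no sentence names it as a covariate.

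Earlier in the same Analysis paragraph, after the description of the arm comparisons, there is an open clause: "we will examine other covariates in the models as necessary, including sex as a biological variable".

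**The concern.** Randomisation makes the arms comparable, so it protects the effect of arm on the mediator. Patients are not randomised to their level of self-efficacy, risk perception or perceived norms, so nothing in the design protects the path from mediator to abstinence. A counterfactual indirect effect needs that path to be free of uncontrolled confounding.

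Covariates for this purpose should be chosen because they may drive both mediator and outcome. The rule stated here instead carries over a list drawn up for effect modification. The earlier score on the same scale is the most obvious candidate confounder: it predicts the later score and may predict quitting in its own right. If it is left out, part of a stable difference between patients can be credited to the intervention's mechanism, and the proportion mediated is overstated. The arm-to-mediator contrast is also estimated less precisely than the collected data allow.

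**Working it through.** **The plan's own figures.** The article gives no figure for the mediation analysis. The sample-size figures reproduce but do not bear on this point. The design effect is 1 + 59 × 0.01 = 1.59, so the effective n is 480/1.59 = 301.9 per arm. With 20% vs 32% and "the significance level of the test is 0.017 after Bonferroni adjustment" taken as two-sided, power is 83.7% against the stated 84%. Enrolment is 1200/(1 − 0.20) = 1500.

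**Inputs assumed, because the documents do not give them.**
- r, the correlation of the mediator between month 0 and follow-up: 0.3 to 0.7.
- g, the direct effect of the month-0 value on abstinence: 0 to 0.4 log-odds per SD.
- Arm effect on the mediator: 0.3 SD.
- b, the follow-up mediator's effect on abstinence: 0.4 log-odds per SD.

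**Bias of the indirect effect.** The model is M1 = r·M0 + 0.3·A + e and logit P(Y) = −1.4 + 0.4·M1 + g·M0 + 0.4·A, with M0 and M1 the month-0 and follow-up scores and A the arm. If M0 is omitted, the coefficient of M1 is approximately b + g·r, so the inflation is approximately g·r/b. A simulation of 400,000 patients, fitted with and without M0, gives:

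| r | g | g·r/b | simulated inflation |
|---|---|---|---|
| 0.3 | 0.2 | 15% | 14% |
| 0.5 | 0.2 | 25% | 25% |
| 0.5 | 0.4 | 50% | 46% |
| 0.7 | 0.4 | 70% | 65% |
| any of these | 0 | 0% | 0% to 2% |

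**Check at trial size.** This used 240 AAA vs 480 AAC patients, 8 centers each, ICC 0.01, r = 0.5, an arm effect of 0.3 SD and 1,500 replicates.
- Mediator real (OR 1.3 per SD): the true indirect OR is 1.082. Without M0 the mean estimate is 1.106, 1.126 or 1.148 for a direct baseline OR of 1.15, 1.3 or 1.5. On the log scale, for example, ln 1.106/ln 1.082 = 1.28 and ln 1.148/ln 1.082 = 1.75, an overstatement of 28% to 75%. With M0 the estimate is 1.082 to 1.083.
- Mediator inert (b = 0): a joint-significance test at nominal 5% rejects in 10.3%, 23.4% or 49.4% of trials without M0, and in 4.5% to 5.4% with it. With no direct baseline effect the rate without M0 is 3.7%.

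**Precision of the arm-to-mediator contrast.** Adjustment multiplies the individual-level variance by 1 − r²: 0.91, 0.75 and 0.51 for r = 0.3, 0.5 and 0.7. At r = 0.5 the standard error falls from √(1/240 + 1/480) = 0.079 to 0.079 × √0.75 = 0.068. A contrast with 80% power moves to Φ((1.960 + 0.842)/√(1 − r²) − 1.960) = 84%, 90% and 98% for the three values of r.

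**The price of adjustment.** If the baseline value has no direct effect on abstinence, power for the indirect effect in the trial-size simulation falls from about 73% to 61%, because the mediator-to-outcome coefficient has a wider standard error.

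No moderators were fitted in either simulation.

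**The case against.** **The rule is not a closed list.** A reader might infer that the models adjust for the moderators and nothing else. The text does not say so: it states what will be included, and the same paragraph allows other covariates. A full covariate list for a secondary analysis may also sit in a statistical analysis plan that is not shown. This stands. What remains is that the article does state a covariate rule and the rule omits the obvious variable. The open clause is only a partial answer: it is framed around balance between arms, and a baseline score can be perfectly balanced and still confound mediator with outcome.

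**Bias is conditional.** A reader might also infer that the indirect effects are confounded as a matter of fact. They are not if the month-0 value acts on abstinence only through the follow-up value. Nicotine dependence, amount smoked and prior quit attempts may absorb part of any confounding. The simulations omit those covariates, so they do not represent the model exactly as planned. The 49% false-positive rate further requires a follow-up score with no effect alongside a baseline score with a direct OR of 1.5.

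**Hypothesis (ii) is not biased.** A reader might take the proportion mediated to be the test of hypothesis (ii). As worded under Hypotheses, that hypothesis says AAC will raise perceived benefits, norms and self-efficacy. This is the arm-to-mediator effect, which randomisation protects.

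**The form of the mediator is not fixed.** The figures above assume a raw follow-up score. With change from month 0 they would not apply. Change scores do not remove the problem, though: the slope of M0 on M1 − M0 is (r − 1)/(2 − 2r) = −0.5, so omitting M0 would bias in the other direction.

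**Month 0 may not precede the intervention.** Under Aim 3 Measures, the baseline patient survey records receipt of AAA or AAC, and Table 3 times this at 0 and 1 month. If the score is taken after the provider's advice, adjusting for it could remove part of the mediated effect. This stands and limits the fix. So does the fact that the provider-level mediator is measured only at the index visit and has no separate baseline value.

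**Conclusion.** The point holds in a limited form. The stated covariate set does not name the month-0 value of the patient-level mediators, although the trial collects it. The indirect effects and proportion mediated can be confounded as a result. The 14% to 65% inflation rests wholly on assumed correlations and effects (r 0.3 to 0.7, g 0.2 to 0.4, b 0.4, no moderators fitted), and the bias vanishes when g = 0.

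The primary abstinence comparison is untouched. The arm-to-mediator contrast in hypothesis (ii) is unbiased but less precise than it could be, by the variance factor 1 − r². The documents do not support saying that the plan excludes the baseline value, or that its mediation results are certain to be biased. This is a worthwhile improvement to a secondary analysis.

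**What to change.** Keep the sentence "All causal models will include moderator variables" and add after it: *Models for the patient-level mediators (risk perceptions, self-efficacy, social norms) will also include the month-0 value of the mediator under study, in both the mediator model and the outcome model, provided it was recorded before the provider delivered AAA or AAC.*

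The wording leaves out the provider-level mediator. The plan should also state whether the month-0 survey comes before or after the provider encounter, since the proviso depends on it.

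No new data are needed. The statistical cost is the drop in power for the indirect effect shown above, from about 73% to 61%, in the case where the baseline value has no direct effect on abstinence.
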